#### Serum sample study

3.4.4

Serum samples from patients in all groups will be drawn from a central vein catheter. Our aim is to analyze this tissue to investigate the relationship between variations in interleukin-6 (IL-6), interleukin-10 (IL-10), tumor necrosis factor a (TNFa), methane dicarboxylic aldehyde (MDA), myeloperoxidase (MPO), total antioxidation capacity (TAOC), total superoxide (TSOD), and clinical presentation of perioperative levels and levels with xenon/oxygen treatment. A better understanding of the key molecular processes and xenon treatment also has the potential of leading to novel treatment therapies.

## Discussion

4

This trial protocol has several aspects that warrant further discussion, as it has an innovative design, and its main concern is xenon's potential organ protection, as outlined in the results of experiments in animals and limited studies in humans.

### Intervention content

4.1

The intervention content for each of the groups was carefully selected. The content of the oxygen group was chosen to represent current practice for this operation. Based on a previous non-randomized controlled clinical trial,^[17]^ pulmonary static inflation with 50% xenon during CPB attenuated OI decreases at the end of surgery; but the effectiveness diminished at 6 hours after surgery and the valid intra-alveolar xenon concentration was only about 25% to 30% of the inhaled 50% xenon concentration. Therefore, a xenon-treatment arm was designed as 3 groups of pulmonary static inflation with 50%, 75%, and 100% xenon, respectively. We suggest that future trials might define appropriate concentration of xenon for the best practice intervention.

### Compliance and loss to follow-up

4.2

There are approximately 300 to 400 cases of AAD surgery performed in the Beijing Anzhen Hospital per year. If 50% of these patients are eligible and consent, we will meet our recruitment target in approximately 1 year. Therefore, we have accounted for a dropout rate of 10% to 15% from the entire study over time. These estimates are based on assessments of our previous study data.^[16]^

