#### Primary outcome measure

2.4.1

The study primary outcome measure is the perioperative change of the patient's oxygenation index (OI) presurgery, at end of surgery, and at 6 hours postsurgery. The oxygenation index is calculated by the arterial oxygen tension (PaO_2_)/inspired oxygen fraction (FiO_2_) ratio, and is a validated and effective measure of oxygen impairment change.

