#### Sample size calculation

3.4.2

The sample size calculation is based on the primary outcome measure, which is the variable of OI at perioperative period. Currently, there is no established minimal clinically important difference (MCID) for the OI. Based on previous study,^[17]^ an approximation to the MCID could be viewed as 38 mm Hg, the standard deviation (SD) of a single OI observation as 70 mm Hg, and the auto-correlation as 0.5. With a 5% (2-sided) type I error rate, based on preliminary experiments, 36 patients per treatment group are necessary, and the power was 0.80048. Assuming a 10% dropout rate, the final sample size will be 160 patients (40 patients/group) (Table 2). (Power Analysis and Sample Size, PASS V11.0, NCSS, LLC; Kaysville, UT).

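### Section 4.2 says a 10% to 15% dropout rate has been accounted for, but the 160 patients in section 3.4.2 cover 10% and nothing above it

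*Protocol article*

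**What the plan says.** Section 3.4.2 (Sample size calculation) bases the trial on the OI. Its inputs are a difference of 38 mm Hg, a standard deviation of 70 mm Hg and an autocorrelation of 0.5, at a two-sided 5% level. It concludes that "36 patients per treatment group are necessary, and the power was 0.80048". It then makes a single allowance for loss: "Assuming a 10% dropout rate, the final sample size will be 160 patients (40 patients/group").

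Section 4.2 (Compliance and loss to follow-up) states that "we have accounted for a dropout rate of 10% to 15% from the entire study over time", and says that its estimates come from the group's own previous study data.

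The abstract and section 3.4.1 give the same target, 160 patients or about 40 per group. No section gives a larger target or a second allowance.

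**The concern.** The two sections describe the same 160 patients but credit them with different tolerances for loss. The figure of 36 is what the plan itself calls necessary, so any loss that takes a group below 36 breaks the plan's own requirement. Section 4.2 presents rates up to 15% as foreseeable from earlier data and as already provided for. A reader, funder or ethics committee relying on 4.2 would think the stated power survives a 15% loss. At stake is the accuracy of a stated property of the sample size, and a small amount of power for the primary outcome.

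**Working it through.** **Inputs, all from the protocol article.** Section 3.4.2: difference 38 mm Hg ("an approximation to the MCID could be viewed as 38 mm Hg"), SD 70 mm Hg ("the standard deviation (SD) of a single OI observation as 70 mm Hg"), correlation 0.5 ("the auto-correlation as 0.5"), two-sided 5% level, 36 required per group, 10% dropout, 40 per group. Section 2.4.1: three measurement times ("oxygenation index (OI) presurgery, at end of surgery, and at 6 hours postsurgery"). Section 4.2: dropout 10% to 15%.

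**Step 1: reproduce the 36.** Assume a two-group comparison of the mean of m = 3 measurements with common correlation 0.5.

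- Effective SD = 70 × √[(1 + 2 × 0.5)/3] = 70 × √(2/3) = 57.15.
- n per group = 2 × (1.960 + 0.842)² × 57.15² / 38² = 35.5, rounded up to 36.
- Power at 36 by the normal approximation is 0.805, close to the printed 0.80048 but not identical.

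This basis gives the plan's required number. It remains a reconstruction, because the body of Table 2 is not available.

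**Step 2: reproduce the 160.** 36/(1 − 0.10) = 40.0 per group, and 4 × 40 = 160. The division is exact, so the largest loss that preserves 36 per group is 1 − 36/40 = 10%.

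**Step 3: apply the range in section 4.2.**

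| Loss | Evaluable per group from 40 | Recruited per group needed to keep 36 |
|---|---|---|
| 10% | 36.0 | 40 (160 total) |
| 12.5% | 35.0 | 36/0.875 = 41.1, so 42 (168 total) |
| 15% | 34.0 | 36/0.85 = 42.4, so 43 (172 total) |

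The cruder rule n × (1 + d) does not rescue the claim: 36 × 1.15 = 41.4, so 42 per group (168 total). Only the lower end of the stated range is met.

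**Step 4: power at 34 per group.** On the basis of Step 1, power = Φ(38/[57.15 × √(2/n)] − 1.960).

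- n = 36: Φ(2.821 − 1.960) = 0.805
- n = 35: 0.794
- n = 34: Φ(2.741 − 1.960) = 0.783

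With the t distribution the values at 36 and 34 are 0.794 and 0.771. The fall is about 2 points either way.

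**Step 5: does the fall depend on the reconstruction?** Very little. With three measurements whose correlation decays over time (first-order autoregressive, effective SD 54.72), power goes from 0.838 at 36 to 0.817 at 34. With two measurements (effective SD 60.62), it goes from 0.758 to 0.734. The level of power differs between these bases, but the step from 36 to 34 costs 2.1 to 2.4 points in all of them. Neither alternative gives 36 as the required number; they give 33 and 40.

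**The case against.** The strongest reply is that the two rates need not describe the same loss. Section 4.2 concerns loss to follow-up and speaks of the whole study over time. Sections 2.6.4 and 3.3 run that follow-up to 12 months, by clinic visit or telephone. The primary OI is complete 6 hours after surgery (section 2.4.1), and section 3.4.2 sizes the trial on it. An allowance of 10% for a 6-hour endpoint and an expectation of 10% to 15% over a year can both be right. This stands as a limit on the consequence: losses after 6 hours do not reduce the power of the primary comparison. It does not remove the inconsistency. The article never separates the two kinds of loss, and 4.2 says the wider range has been accounted for when the only accounting shown is for 10%.

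A second reply is that two patients per group and about two points of power are minor. That is correct, and it argues for a light correction, but the sentence in 4.2 is still wrong as written.

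A reader might also infer something larger: that power at 15% loss is only 0.73, or that 160 patients cover no dropout at all. That inference starts from the observation that the printed 0.80048 is what the normal formula gives for two measurements at 40 per group. The documents do not support using it here. On that basis the required number would be 40, against the 36 that section 3.4.2 states. Most of the apparent fall, from 0.800 to 0.758, would then come from that separate discrepancy and not from dropout. Without the body of Table 2 it cannot be settled which calculation was run.

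**Conclusion.** The point holds as a mismatch between two statements. The 160 patients cover 10% loss exactly, and no part of the 10% to 15% range above its lower end is covered. At 15% each group has 34 evaluable patients, two fewer than the plan requires; covering that rate would need 43 per group, 12 more patients in all.

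The size is modest. If the full 15% applied to the primary OI, power would be about 0.78 instead of about 0.80, assuming the mean of three measurements, SD 70 and common correlation 0.5. It would be nearer 0.80 to the extent that the extra loss occurs after 6 hours. A reader might infer that the trial is seriously underpowered for its primary outcome on this account; a difference of two points, under a loss rate that may not apply to that outcome, does not support this. The correction is worth making because the statement concerns a key design property and is cheap to put right.

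**What to change.** 1. In section 4.2, replace the claim about 10% to 15% with a statement that 160 patients cover 10% loss of the primary endpoint only.
2. In the same place, say whether the 10% to 15% expected from earlier data refers to missing 6-hour OI values or to loss during the 12-month follow-up. Only the former bears on the primary power.
3. In section 3.4.2, add the power at 34 evaluable patients per group, taken from the sponsor's own calculation. On the reconstruction above it is about 0.78.

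The cost is two or three sentences and a slightly less favourable stated power. Neither more patients nor a different primary analysis is needed to resolve this mismatch. If the sponsor prefers to keep the claim that 15% is covered for the primary endpoint, the target would have to become 172.

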### Interpretation

4.3

The importance of highlighting potential outcomes and clinical implications has been shown by the development of this trial. If each concentration of xenon-treatment is shown to be no more effective than nitrogen-control, then the continued use of xenon for this condition and in a wider context should be terminated. Conversely, if 50% xenon (or 75% xenon or 100% xenon) is shown to be an effective treatment, then the current xenon-treatment for the procedure should be encouraged. If 100% xenon is more effective than 50% xenon, then it will have been confirmed that the effectiveness of xenon is based on concentration. If a comparison of 100% xenon with 50% xenon demonstrates no difference in primary outcome, then there are health care economic implications, and a cost utility analysis will be performed for future procedures.

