### Design of trial

2.2

The trial is a 4-group, parallel, RCT, which has been registered at www.clinicaltrials.gov (Identifier: NCT02468531). By performing 4 2-way comparisons, we will test differences between groups. Patients will be randomized in a 1:1:1:1 ratio. Blinding will be performed for patients, post intervention assessors, statisticians, and investigators.

The null hypothesis for this trial is that there is no difference in protection effects between nitrogen and xenon in patients with postoperative oxygen impairment. The patients who receive nitrogen are the control group in this comparison. If this null hypothesis is rejected, then inhaled xenon may be an effective treatment. If this null hypothesis is not rejected, then inhaled xenon may be ineffective.

However, there is also a need to understand how potential treatment differences are achieved, and/or if different concentrations of inhaled xenon produce similar effects. Further comparisons, including the use of a control intervention, can provide this information.

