#### Analysis of endpoints

3.4.3

The statistical analysis of the study is the responsibility of the trial statistician. Baseline data will be compared to determine whether or not there are any clinically important differences between treatment and control groups that have occurred by chance. The analysis will be performed by SPSS statistical software (SPSS for Windows, V.18.0; Chicago, IL).

All statistical testing will be performed at the 2-sided 5% significance level, and 95% confidence intervals will be presented where appropriate. For all analyses, the appropriate model assumptions were verified, and alternative methods used if more appropriate. Prior to any analysis, any missing data patterns will be investigated, the reasons for missing data obtained and summarized where possible. The primary analysis, such as OI, inflammatory cytokines, and ROS, will be conducted on the repetitive measurement and analysis of variance. The intubation time will be summarized descriptively using median, interquartile ranges and ranges overall, as well as by treatment arm. Complications between the trial arms will be compared in terms of frequency and severity. Cross-tabulations will be generated to relate complications to treatment, and chi-squared tests will be used to assess the significance of the association. A receiver operating characteristic (ROC) curve will be used to test discrimination of the treatment model. A *P* value <.05 will be considered statistically significant.

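### The rule for abandoning xenon can be met by three non-significant comparisons whose confidence intervals still contain the 38 mm Hg target, and it reaches beyond what the trial studies

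*Protocol article*

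**What the plan says.** Section 4.3 (Interpretation) sets out in advance what each result will mean. If every one of the three xenon concentrations is shown to be no better than nitrogen, "then the continued use of xenon for this condition and in a wider context should be terminated". If any concentration works, xenon treatment is to be encouraged. A further rule begins "If a comparison of 100% xenon with 50% xenon demonstrates no difference in primary outcome" and leads to health-economic implications and a cost utility analysis.

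Section 2.2 (Design of trial) states a null hypothesis of no difference between nitrogen and xenon, and is more guarded: "If this null hypothesis is not rejected, then inhaled xenon may be ineffective".

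The testing framework is in section 3.4.3: "All statistical testing will be performed at the 2-sided 5% significance level, and 95% confidence intervals will be presented where appropriate". The sample size (section 3.4.2) rests on these statements: "an approximation to the MCID could be viewed as 38 mm Hg", "the standard deviation (SD) of a single OI observation as 70 mm Hg", an autocorrelation of 0.5, and "With a 5% (2-sided) type I error rate, based on preliminary experiments, 36 patients per treatment group are necessary, and the power was 0.80048". The article states no equivalence or futility margin, and does not link the rules in 4.3 to the confidence interval or to the 38 mm Hg target.

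**The concern.** A superiority test that fails to reject does not show absence of benefit. It shows that the data did not exclude zero. Whether they exclude a worthwhile benefit depends on the upper confidence limit, which the rule in 4.3 does not use. With no margin stated, non-significance in all three comparisons is the only route the article offers to the conclusion that xenon is no better than nitrogen. A set of results compatible with the plan's own important difference could therefore trigger a recommendation to stop using xenon.

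The reach of the recommendation is a separate fault and needs no calculation. The primary outcome is the oxygenation index (OI) up to 6 hours after surgery (section 2.4.1), in type A dissection surgery at one centre, in patients aged 18 to 65 with many exclusions (sections 2.5.1 and 2.5.2). The Key Points concede that applicability to other centres is limited. The Introduction lists anesthetic, neuroprotective and cardioprotective roles for xenon that this primary outcome does not test.

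The rule for 100% against 50% xenon has the same logical gap: no margin says when two concentrations count as not different.

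**Working it through.** **Inputs (sections 2.4.1, 3.4.2, 3.4.3).** Target 38 mm Hg; SD of one value 70; correlation 0.5; three OI measurements; two-sided 5%; 36 evaluable per group.

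**Reproducing the plan's figure.** Take the contrast as the mean of three equally correlated measurements. This is an assumption, chosen because it returns the stated size.
- Effective SD = 70 × √((1 + 2 × 0.5)/3) = 57.15.
- n = 2 × (1.96 + 0.8416)² × 57.15² / 38² = 35.5, so 36 per group.
- Power at 36 = 0.805 by the normal formula and 0.794 by the t-based one; the plan states 0.80048.
- 36/0.9 = 40 per group, as stated.

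**Precision at 36 per group.**
- SE = 57.15 × √(2/36) = 13.47.
- 95% half-width = 1.96 × 13.47 = 26.4 mm Hg.
- An estimate is non-significant in favour of xenon if below 26.4. Its interval still contains 38 if it is at least 38 − 26.4 = 11.6. Estimates from 11.6 to 26.4 meet both conditions.

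**How often the rule would be met.** The rule needs all three comparisons to be null, so the three contrasts were simulated together with the shared nitrogen group (400,000 runs). The last column is the product of the two before it.

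| True benefit in the three arms (mm Hg) | All three non-significant | Of these, at least one interval contains 38 | Both |
|---|---|---|---|
| 0, 0, 0 | 88% | 36% | 32% |
| 10, 10, 10 | 75% | 62% | 46% |
| 19, 19, 19 | 48% | 80% | 38% |
| 0, 0, 38 | 17% | 90% | 15% |
| 38, 38, 38 | 5% | 97% | 5% |

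**Sensitivity.**
- 40 per group (no dropout): half-width 25.1. Among all-null trials, at least one interval contains 38 in 29% at zero effect and 75% at 19 in every arm.
- SD 70 (one time point or a change score), 36 per group: half-width 32.3. The corresponding figures are 62% and 91%.

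**100% against 50% xenon.** The SE is the same, 13.47. A true difference of 19 mm Hg would be non-significant in about 71% of trials.

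**The case against.** The strongest reply is that this is Discussion text. It changes no test, data set or estimate. Section 3.4.3 promises confidence intervals where appropriate, and section 4.4 promises CONSORT reporting, so imprecision should be visible to readers. This limits the harm, but the intervals have no role in the rule as written.

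Several stronger readings are tempting, and the article does not support them.

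- **That one non-significant comparison leads to abandonment.** Section 4.3 requires every concentration to fail. The 20% chance of missing a true 38 mm Hg effect in a single arm is therefore not the error rate of this rule. The relevant figures are 5% if all arms give 38 and 17% if only one does.
- **That the article treats a null result as proof.** It does not use that word. Section 2.2 says only that xenon may be ineffective, so it does not repeat the fault. Section 4.3 asks that lack of superiority be shown. Taking that to mean non-significance is an inference, though the only workable one without a margin.
- **That the interval would usually contain 38 whatever the truth.** If xenon is inert, this happens in 36% of all-null trials, a minority.
- **That the article draws economic conclusions from a null dose comparison.** It mentions implications and a further analysis.

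It is also fair to say that 38 mm Hg is only approximate: section 3.4.2 acknowledges that no minimal important difference is established.

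**Conclusion.** The point holds as a fault in the stated interpretation rule. Section 4.3 permits a firm negative recommendation on evidence that can remain compatible with the plan's own target, it is stronger than section 2.2, and its reach beyond this condition conflicts with the Key Points caveat. The size depends on the truth. A uniform benefit of half the target would meet the rule in about 48% of trials, and four in five of those would still have 38 mm Hg inside at least one interval. Benefit at only one concentration would meet it in about 17%, with 38 still inside in nine of ten. A modest average effect is plausible, since section 4.1 reports that the earlier benefit of 50% xenon had diminished by 6 hours.

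These figures rest on the plan's SD and correlation, normal theory, and a contrast averaged over three measurements. The last is inferred from the reproduced sample size, not stated. The objection to the wider reach rests on none of them.

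**What to change.** Reword section 4.3 and align it with section 2.2.

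1. Conclude lack of benefit on OI only if the upper 95% confidence limits of the benefit over nitrogen lie below 38 mm Hg for all three concentrations. Otherwise call the result inconclusive.
2. Delete the extension to wider use, and limit the conclusion to perioperative OI in the population studied.
3. Do not read a non-significant comparison of 100% with 50% xenon as no difference. Report its confidence interval, and claim similarity only against a prespecified margin smaller than 38 mm Hg. A margin of 38 would equal the whole target difference, so concentrations almost that far apart could pass as similar.

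The change needs no additional patients and no change in trial conduct. The cost is more results reported as inconclusive: about 36% of all-null trials even if xenon is inert. Similarity will also be hard to claim. With a half-width of 26.4 mm Hg, a 95% interval cannot fit inside any margin below 26.4, and even at ±38 two truly identical concentrations would qualify only about 61% of the time. The trial is not sized for that question, and the text should say so.

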### Nitrogen group (control group)

2.8

The nitrogen arm is the surgical comparison group. The procedure will be performed while the patient is under general anesthesia. After routine intubation, 50% nitrogen/50% oxygen will be inhaled for 1 hour, and then 100% oxygen continued until cardiopulmonary bypass (CPB) is performed. After the aorta is cross-clamped and mechanical ventilation stopped, the lungs will be inflated with 50% nitrogen/50% oxygen to maintain a mean airway pressure. Pulmonary static inflation will be stopped 15 minutes before aortic declamping and cardiac resuscitation. One hour after the end of CPB, 50% nitrogen/50% oxygen will be inhaled for 1 hour, and then 100% oxygen will be continued until the end of surgery. These measures provide the oxygen group with the characteristics necessary to provide a reasonable comparison and to account for the placebo effects of surgery.

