### Xenon group

2.9

The procedure will be performed with the patient under general anesthesia. After routine intubation, 50% xenon/50% oxygen will be inhaled for 1 hour, and then 100% oxygen continued until CPB is performed. One hour after the end of CPB, 50% xenon/50% oxygen will be inhaled for 1 hour, and then 100% oxygen will be continued until the end of surgery.

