#### 50% xenon group:

2.9.1

After the aorta is cross-clamped and mechanical ventilation is stopped, the lungs will be inflated with 50% xenon/50% oxygen to maintain a mean airway pressure. Pulmonary static inflation will be stopped 15 minutes before aortic declamping and cardiac resuscitation.

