#### 75% xenon group:

2.9.2

After the aorta is cross-clamped and mechanical ventilation stopped, the lungs will be inflated with 75% xenon/25% oxygen to maintain a mean airway pressure. Pulmonary static inflation will be stopped 15 minutes before aortic declamping and cardiac resuscitation.

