#### 100% xenon group:

2.9.3

After the aorta is cross-clamped and mechanical ventilation stopped, the lungs will be inflated with 100% xenon to maintain a mean airway pressure. Pulmonary static inflation will be stopped 15 minutes before aortic declamping and cardiac resuscitation.

The OI will be recorded before the operation, at end of surgery, and 6 hours postoperatively. OI will be calculated based on an FiO_2_ of 100%, a PEEP of 5 cm H_2_O, a tidal volume of 8 mL/kg, an inspiratory/expiratory ratio of 1:2, and a respiratory rate of 10 times per minute.

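### Among the xenon arms, inflation oxygen falls exactly as xenon rises, so 100% versus 50% xenon can neither confirm nor rule out a xenon concentration effect

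*Protocol article*

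**What the plan says.** The protocol article sets the static-inflation gas arm by arm.

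- Control (section 2.8): "the lungs will be inflated with 50% nitrogen/50% oxygen to maintain a mean airway pressure".
- 50% xenon (section 2.9.1): "the lungs will be inflated with 50% xenon/50% oxygen to maintain a mean airway pressure".
- 75% xenon (section 2.9.2): "the lungs will be inflated with 75% xenon/25% oxygen to maintain a mean airway pressure".
- 100% xenon (section 2.9.3): "the lungs will be inflated with 100% xenon to maintain a mean airway pressure".

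Outside the inflation period the three xenon arms are treated alike. Section 2.9 gives all of them the same gas before bypass, "After routine intubation, 50% xenon/50% oxygen will be inhaled for 1 hour, and then 100% oxygen continued until CPB is performed", and again afterwards: "One hour after the end of CPB, 50% xenon/50% oxygen will be inhaled for 1 hour". The control follows the same timetable with nitrogen in place of xenon.

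Section 2.2 states the null hypothesis as nitrogen versus xenon and adds that further comparisons can show whether different xenon concentrations act alike. Section 4.3 then fixes how results will be read. If 100% xenon does better than 50% xenon, "then it will have been confirmed that the effectiveness of xenon is based on concentration". If the two do not differ on the primary outcome, the article draws economic implications and plans a cost-utility analysis. No part of the article mentions that oxygen differs between the arms during inflation.

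**The concern.** In the xenon arms the inflation mixture contains only xenon and oxygen, so raising one lowers the other by the same amount. The arms are labelled by xenon concentration, but each step up is also a step down in oxygen. Section 4.3 credits the whole difference to xenon.

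The article's own outcomes are ones that lung oxygen might plausibly influence: PaO2/FiO2 as the primary outcome (section 2.4.1), with reactive oxygen species and inflammatory cytokines as secondary outcomes (section 2.4.2). An oxygen effect could therefore be published as a xenon dose-response, or could cancel a real one and be read as no difference. The stated rule invites both mistakes. Neither a larger sample nor a more detailed analysis plan would prevent them, because the ambiguity lies in the arms being compared.

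**Working it through.** **Gas fractions during static inflation** (sections 2.8, 2.9.1 to 2.9.3)

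| Arm | Xenon % | Oxygen % | Nitrogen % |
|---|---|---|---|
| Control | 0 | 50 | 50 |
| 50% xenon | 50 | 50 | 0 |
| 75% xenon | 75 | 25 | 0 |
| 100% xenon | 100 | 0 | 0 |

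**What each contrast changes, in percentage points**

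| Contrast | Xenon | Oxygen | Nitrogen |
|---|---|---|---|
| 50% v control | +50 | 0 | -50 |
| 75% v control | +75 | -25 | -50 |
| 100% v control | +100 | -50 | -50 |
| 100% v 50% | +50 | -50 | 0 |

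**Can xenon and oxygen be separated?** In the three xenon arms, oxygen = 100 - xenon. The correlation is -1.00, and a design matrix with an intercept, xenon and oxygen has rank 2 of 3. The two effects are not separately estimable from those arms.

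Across all four arms:

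- Deviations from the mean are (-56.25, -6.25, 18.75, 43.75) for xenon and (18.75, 18.75, -6.25, -31.25) for oxygen.
- r = -2656.25 / sqrt(5468.75 × 1718.75) = -0.87.
- Variance inflation = 1/(1 - r²) = 4.0.
- A xenon slope can then be computed, but only by assuming linear, additive effects and no nitrogen effect. With nitrogen added, the matrix has rank 3 of 4.

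**The plan's sample size, reproduced.** Inputs from section 3.4.2: difference 38 mm Hg, SD 70 mm Hg, correlation 0.5, two-sided 5%. Three measurement times come from section 2.4.1.

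- SD of the mean of three equally correlated measurements: 70 × sqrt((1 + 2 × 0.5)/3) = 57.15.
- n per group = 2 × (1.960 + 0.842)² × 57.15² / 38² = 35.5, rounded up to 36, as stated.
- Power at 36 is 0.805 (normal approximation) or 0.794 (noncentral t), against 0.80048 stated.
- 36/0.9 = 40 per group, 160 in total.

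These figures are not in dispute; they set the scale for the next step.

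**Illustration under an assumption.** The documents give no oxygen effect. Suppose xenon concentration has no effect, and moving inflation oxygen from 50% to 0% shifts the oxygenation index by d, in either direction. The standard error of the 100%-versus-50% difference is 57.15 × sqrt(2/36) = 13.47. The chance of a significant result is Φ(|d|/13.47 - 1.96) + Φ(-|d|/13.47 - 1.96).

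| Assumed shift d (mm Hg) | Chance of a significant result |
|---|---|
| 0 | 5% |
| 19 | 29% |
| 38 | 81% |

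An oxygen effect opposing a real xenon effect would hide it by the same mechanism.

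**The case against.** Several counter-arguments have force.

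- *Randomisation protects the comparisons.* It does: each contrast is a fair comparison of the mixtures as given. What fails is crediting the result to xenon or its concentration.
- *The main null hypothesis has a clean test.* It does. 50% xenon and nitrogen match on oxygen before, during and after bypass.
- *In a two-gas mixture, more xenon must mean less oxygen.* True. That explains the arms, but it does not support the word *confirmed*.
- *Direct carry-over into the outcome is unlikely.* After bypass all arms share one oxygen schedule, and the oxygenation index is calculated at fixed ventilator settings with FiO2 of 100% (section 2.9.3). This is a fair limit. A biological effect of inflation oxygen remains possible, and its size is unknown.
- *The article leaves the best concentration to future trials* (abstract and section 4.1). That hedge does not reach section 4.3, which states its rule without qualification.

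A reader might also infer more than the documents support:

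- That 75% and 100% xenon versus control say nothing about xenon. Those arms also receive oxygen-matched xenon before and after bypass, so only the inflation part of each contrast is mixed.
- That the rule for abandoning xenon rests on confounded contrasts. It requires every concentration to fail, including the oxygen-matched 50% arm.
- That three of the four planned comparisons are affected. Section 2.2 announces four two-way comparisons but never lists them, so no such count can be made.
- That no analysis of the trial could separate the gases. That is exact for the xenon arms; over four arms a separation exists, but only under strong assumptions that the article does not state.

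**Conclusion.** The concern holds for the interpretation, not for the arms or the sample size. A 100%-versus-50% difference cannot confirm that effectiveness depends on xenon concentration, and no difference cannot rule out such dependence, because a 50-point rise in xenon comes with a 50-point fall in oxygen. This follows from the stated mixtures and needs no outside assumption. The 75% and 100% comparisons with control carry the same mixture during inflation, with oxygen lower by 25 and 50 points. Only 50% xenon versus nitrogen is oxygen-matched throughout.

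How far this would distort results is unknown. The 29% and 81% figures depend on assumed oxygen effects and show only that an effect no larger than the planned difference would be enough to mislead. It would go too far to say that an observed gradient would be an oxygen artefact: the documents give neither size nor direction, so bias could go either way.

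**What to change.** Leave the arms as they are and change the claims.

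1. In section 4.3, replace the sentence on 100% versus 50% xenon with a statement that any difference among the xenon arms may reflect xenon, oxygen or both.
2. In the same section, say that the 100%-versus-50% result, including a finding of no difference, compares two gas mixtures, and attach that caveat to the cost-utility consequence.
3. In sections 2.2 and 4.3, name 50% xenon versus 50% nitrogen as the oxygen-matched test of xenon, and describe 75% and 100% xenon versus control as comparisons of gas mixtures.

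This takes a few sentences and alters no treatment, endpoint, test or sample size. The price is that the trial gives up its claim to establish a xenon dose-response.
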